#### Game Evaluation: Serious Game Usability and Engagement

To assess the usability of the game, we defined usability as “the extent to which a product can be used by specified users to achieve specified goals with effectiveness, efficiency and satisfaction in a specified context of use” [24]. According to the literature [25], usability testing is important for the serious game, particularly those designed for heterogeneous populations, including individuals that may not be accustomed to interacting with new technologies (ie, “nongamers”).

Among all the procedures described in literature [26], two main approaches assess usability: an observational analysis, in which a user interacts with the system while the developers observe and note every significant player-game interaction or player’s comment, and a survey-based analysis, in which the user fills out evaluation questionnaires after the game session [27-29]. Although several scales have been developed (eg, the System Usability Scale [30] and the Questionnaire for User Interaction Satisfaction [31]), there are no validated scales to assess games usability thus far. Therefore, we decided to perform a mixed method combining observational analysis of participants and a self-report questionnaire—the Game Experience Questionnaire—to partially overcome the current limitations of both quantitative methods [32].

**Figure 8 figure8:**
[figure not shown]
During the game, the player carefully chooses Eugene’s diet to maintain correct nutrition habits.

**Figure 9 figure9:**
[figure not shown]
During Gene Adventure, the player carefully manages Eugene’s physical activity to maintain a good lifestyle.

The observational analysis will record participants’ reactions during the game, with a particular focus on their comments and emotional reaction (laugh, groan, frustration, doubts on how to proceed, etc), to gain real-time information that may not be captured by posttest surveys [33]. The observational analysis will provide information on the overall engagement of the player: Deep engagement in serious games has been associated with learning and students’ academic achievements [34,35].

Engagement refers to a holistic experience or mixture of involvement and enjoyment; it is a key factor for serious games and determines the effectiveness of learning. In previous studies, several measures such as scales of immersion and presence [36], flow [37], and engagement [38] have been applied for different aspects of engagement in serious games. The most-appropriate questionnaire for our serious game is the Game Experience Questionnaire [39] because it measures how players feel during the game session. This questionnaire comprises 33 items and assesses 7 core dimensions: immersion, flow, competence, positive effect, negative effect, tension, and challenge. For each item, participants state their personal experience on a 5-point Likert scale (from 0 indicating not at all to 5 indicating extremely).

#### Target Population and Recruitment

The pilot usability study will be conducted with a convenience sample of 30 participants. All participants will be recruited by e-mail through the students’ institutional mailing list of the University of Milan (Italy; Master Course in Cognitive Science) and via authors’ acquaintances. The e-mail invitation will entail a brief description of the tasks, the medium amount of time required, and the contact information of the experimenter. All the experimental sessions will be conducted in a quiet room at the University of Milan in the presence of an experimenter.

Considering the heterogeneity of potential users, we will enroll 10 participants and categorize them into 2 groups in each game: one group of 5 “young” participants, aged 16-30 years (major users, includes people who play games more frequently), and another group of 5 “middle-aged” participants, aged 31-65 years (minor users of video games). It is important to assess the usability of both age groups since the potential users of our serious game are individuals of all ages.

#### Method and Procedures

Participants will be assigned to one of the three games and will play the game individually. Before interacting with the game, they will complete an informed consent form. Participants will be briefly instructed about the game and prompted to play on their own without any further direction or instruction. In addition, they will be asked to speak loudly during the game in order to communicate their thoughts. At the end of the play session, participants will report any issue, negative or positive, that they encountered during the game and will be invited to complete the Game Experience Questionnaire. The programmers will dedicate time to address and fix the negative issues.

#### Data Analysis

All data on player usability collected from the observational analysis will be examined using text analysis for qualitative data, as reported previously [40]. The negative issues that could compromise the usability of the serious game will be classified on the basis of the usability heuristics developed by Bertini et al [41] (eg, consistency and mapping, ease of input, screen readability and glancability, flexibility, efficiency of use, and personalization) [42]. Nonparametric statistical analysis for quantitative data will be applied to the Game Experience Questionnaire, with group comparisons based on age and technological expertise (gamers vs nongamers; computer and mobile technology users vs nonusers). Statistical analysis will be conducted using the SPSS Software (version 22; IBM Corp, Armonk, NY), with an alpha value of .05 set a priori for all analyses.

### Substudy 2

#### Game Evaluation: Knowledge-Transfer Test

We will assess participants’ learning outcomes to verify the effectiveness of serious games. Most studies evaluated the effectiveness of serious games through the use of pre- and posttest evaluations [43], whereas some studies used a control group of individuals who received the target information through other instructional techniques. We used both assessment methods.

#### Target Population and Recruitment

To test whether the learning goals were achieved, 60 teenagers and adults aged 16-65 years who volunteer to participate will be enrolled: 30 participants will be assigned to the experimental group and 30 participants, to the control group. Both groups will be age- and gender-matched. All participants will be recruited from the general population by using the author’s e-mail and social media contacts, posters emailed to all University of Milan staff and students, and personal invitations and snowball sampling. The invitation will contain a brief description of the tasks, the median time required, and contact information. All the experimental sessions will be conducted in a quiet room at the University of Milan under the supervision of an experimenter.

#### Materials and Procedures

Before starting the game session, participants will complete a demographic questionnaire on age; gender; education level; previous experience with computer, mobile, or tablet devices; and habits of playing video games. Participants with no experience with technological devices will be excluded.

Participants enrolled (experimental and control groups) will complete the following steps: (1) knowledge-transfer pretest questionnaire, (2) self-efficacy pretest questionnaire, (3) serious game-playing session or paper-based information reading, (4) knowledge-transfer posttest, and (5) self-efficacy posttest.

First, an ad-hoc questionnaire will be used to assess genetic topic-specific knowledge, with questions on Mendel’s laws, mutations, and genetic risk implications. The questionnaire comprises multiple-choice questions or true or false questions such as “From a pair of rabbits with Cc and cc genotype respectively, what is the proportion of their children's genotypes: (A) three CC rabbits and one Cc (B) three Cc rabbits and one (CC) two Cc rabbits and two cc (D) four rabbits cc” or “A healthy lifestyle can prevent or lessen the negative consequences of having genetic predispositions to some diseases (True/False).” Participants that correctly answer more than 80% of the questions in the pretest will be excluded from the study, due to the high base-rate literacy in genetics and genetic risk information. Data will be collected using the Lime Survey [44] in a supervised setting in a quiet room at the University of Milan under the supervision of an experimenter.

Second, a questionnaire will be used to assess perceived self-efficacy with regard to knowledge of genetics, defined as confidence in one’s ability to use genetic information. The questionnaire comprises 8 items, 5 of which are taken from the Self-Efficacy Scale in Carrere et al [45] and include items such as “I am able to understand information about how genes can affect my health” and “I am able to explain to others how genes affect one’s health.” In addition, we added one item to assess the perceived knowledge on the interaction of lifestyle and genetic makeup: “I have a good idea about how my own behaviors might interact with my genetic makeup in affecting my health.” These six items are to be answered on a 7-point Likert scale. Further, we added two items to assess the “task-specific” self-efficacy, that is, the self-efficacy participants experienced in answering the knowledge-transfer questionnaire. Self-efficacy is a precursor to the adoption of health-related behaviors [46]. We included its assessment in this protocol, because it is the only measurable parameter to verify the efficacy of serious games in promoting changes in behaviors in our study (we are unable to directly verify participants’ changes in health-related behaviors and decision-making abilities in the light of the new knowledge). Due to the Dunning-Kruger effect [47] (a cognitive bias of illusory superiority), individuals with low literacy in genetics may mistakenly deem their confidence levels to be higher than their actual levels; however, we will be able to match each participant’s expected and real performance, as we will assess their effective knowledge by using the knowledge-transfer questionnaire.

#### Data Analysis

For knowledge-transfer analysis, the Cohen *d* effect size will be calculated. Statistical analysis will be conducted using the SPSS Software (version 22; IBM Corp), with an alpha value of .05 set a priori for all analyses.

## Results

In 2017, we collected evidence of game usability. Data have been submitted to the 6th International Conference on Serious Games and Applications for Health by the Institute of Electrical and Electronics Engineers 2018 [42] and used to improve game design. Knowledge-transfer testing will begin in 2018, and we expect to collect data on the learning outcomes of serious games in December 2018.

## Discussion

### Overview

Since the launch of the Human Genome project in 1990, there has been a need to improve genetic literacy among the general public [48]. Overall, genetic literacy refers to the understanding of basic biological mechanisms (eg, knowledge that DNA is an informative molecule and determines our variation and diversity); the personal and health implications of genetics; and the interaction and interdependence of genes, the individual, and the environment [49].

Unfortunately, even well-educated people lack an understanding of these concepts [50,51]. Due to the increasing impact of genetic testing [52] and the importance of decision making in disease prevention, it is crucial to educate people about genetics. Without such knowledge, individuals are more likely to make uninformed decisions or handover all decisions on genetic testing to their doctors.

Technological innovations such as serious games might become valid instruments to support public education and empowerment [50,53-55] and prepare citizens for informed personal and societal decision making in genetics.

Our main endpoint will demonstrate if the use of serious games increases people’s knowledge about genetic mechanisms (eg, prototypes for heredity and mutation) and multiple genetic, behavioral, and environmental factors that contribute to the risk of onset of complex diseases such as heart disease (prototype first scenario in Gene Adventure).

We aim to develop an accessible and simple instrument by representing genetic concepts in an appealing narrative that respects the skills of the general population. With our prototype of Gene Adventure, people can experience, in a simulated life, the management of complex information such as genetic risk and develop a deeper understanding of genetics from experience. If this study proves the efficacy of serious games, the developed serious game could be used in combination with other traditional protocols for genetic counseling to spread awareness for decision making in medical genetics.

### Limits and Future Proposal

This study is designed to test “learning” with reference to information acquisition. The pre- and the posttest questionnaires will measure the performance of correctly answering questions based on new information acquired through the serious game. Further, based on our protocol results, we will test another aspect of learning: the ability to apply newly acquired knowledge in unknown situations by, for example, creating a new scenario in which participants will be asked to make decisions about their own health based on the genetic (risk) issues.

Although there are several other interesting and related themes such as knowledge integration (the ability to integrate information on a given subject derived from different perspectives in a coherent mental representation) [56], this study is not designed to investigate them. At present, our experimental protocol is not sufficiently equipped to differentiate the contribution of each serious game in creating the final mental representation of genetic concepts. However, this study will provide some evidence for this issue through differences between the pre- and posttest performances, which will identify the concepts that participants have understood well, and their achievements during the Gene Adventure game, which will indicate how the users apply their knowledge to increase or decrease their character’s health.

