
#### Adventure Game

Gene Adventure, the World of Tomorrow, is an adventure game, wherein the player embodies a young adult named Eugene who lives his everyday life after undergoing DTC genetic testing (Figure 5a). The game takes place in a small city with several facilities (markets, restaurants, pubs, parks, etc). The dramatic curve of Eugene’s story guides the player through several events and answers the “why” of the game, stimulating involvement and motivation. During the game, Eugene learns about the presence of some gene variants and his risk of developing cardiovascular diseases (Figure 5b).

Unfortunately, he cannot manage this information. He is given several chances to obtain clarifications about the implications of the genetic result and its consequences on his health. The player must help Eugene find the best way to manage his cardiovascular risk by accomplishing several subtasks, making health-related decisions (Figure 6), modulating his lifestyle, and interacting with other characters.

The player is given three options for every choice throughout the game session, which are incorporated into the avatar’s behaviors, and each option is assigned a score as follows: –1 for the unhealthy choice, 0 for the neutral choice, and +1 for the healthy choice. The chosen option is simultaneously translated into clear feedback as a modification of the color and expression of a “smile icon,” which represent Eugene’s health state and quality of life (Figure 7).

The three alternatives for each choice are formulated to reflect either recurring behaviors (habits) or occasional behaviors (occurrence) to show that some behaviors could be problematic if repeated over time, and other behaviors are problematic even they are occasional.

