### In-Game Assessment of Knowledge Transfer and Learning Progress

Play-based assessment is implemented through an algorithm that allows us to record changes in the player’s decision-making ability and progress (how they accumulate points and experience and face new issues) during the adventure game session. The system tracks the players’ choices, and the final score is converted into informative and evaluative feedback that is presented to the player at the end of the game session. Based on her or his performance, the player receives positive, intermediate, or negative feedback on 4 aspects: nutrition (Figure 8), physical activity (Figure 9), risk behaviors, and stress management and social interactions.

A composite description of the player’s performance, its implications for health, and a final informative summary of genetic risk management constitute the end of the educational journey. Each game session for a first-time player should last for approximately 30 min.

### Substudy 1

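### The Gene Adventure score is offered as a sign of knowledge transfer and applied knowledge, but with no pre-game or control value it can only describe play

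*Protocol article*

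**What the plan says.** Under Game Description, Adventure Game, the article states: "The player is given three options for every choice throughout the game session". The options are scored −1, 0 and +1 for unhealthy, neutral and healthy, and each choice at once changes a smile icon that shows the avatar's health state.

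The section headed "In-Game Assessment of Knowledge Transfer and Learning Progress" says that play-based assessment uses "an algorithm that allows us to record changes in the player’s decision-making ability and progress". The final score is turned into feedback to the player on four aspects: "nutrition (Figure 8), physical activity (Figure 9), risk behaviors, and stress management and social interactions".

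The Discussion (Limits and Future Proposal) says the study will give some evidence on what each game contributes. One source is the pre/post test differences. The other is players' achievements: "their achievements during the Gene Adventure game, which will indicate how the users apply their knowledge to increase or decrease their character’s health".

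Substudy 2, Materials and Procedures, explains why self-efficacy is measured: "we are unable to directly verify participants’ changes in health-related behaviors and decision-making abilities in the light of the new knowledge". The same section sets the order of events: knowledge and self-efficacy pretests, then the games or the leaflets, then the two posttests. In the game arm, Gene Adventure comes after the two mini-games.

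**The concern.** To show that something was learned or applied, a measure needs a reference: the same measure before teaching, or the same measure in people taught another way. The Gene Adventure score has neither. Its scoring rule rewards the healthier option, and its reporting domains are general lifestyle ones in which most adults already hold views. A good score may therefore reflect what the player brought to the session.

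A rise in score during the session does not settle the matter either. Each choice is followed by visible feedback, so a player can improve by learning which answers the game rewards.

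At stake is one supportive statement in the eventual report. Followed as written, the plan would allow a statement that players applied genetic knowledge, or changed their decision-making, on data that cannot show it.

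**Working it through.** The document gives no figure for this score: no number of choices, no feedback cut-offs, no expected mean. There is nothing to reproduce. The check is one of identification, followed by an illustration.

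**Step 1. What the design supplies**

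| Measure | Game arm, before | Game arm, after | Control, before | Control, after |
|---|---|---|---|---|
| Knowledge questionnaire | yes | yes | yes | yes |
| Self-efficacy questionnaire | yes | yes | yes | yes |
| Gene Adventure score | no | one session, after the mini-games | no | no |

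The questionnaires allow a difference in change between arms. The game score allows no difference of any kind.

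**Step 2. Why one value is not enough**

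Treat the score as the sum of K choices, each worth +1, 0 or −1 with probabilities pH, pN and pU. The simple sum is an assumption, because the algorithm is not given. Then the expected score is K × (pH − pU). Take K = 20 (assumed) and two players:

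- Player A chose at 50/30/20 (healthy/neutral/unhealthy, in %) before the session and learned nothing. Expected score: 20 × (0.50 − 0.20) = +6.
- Player B would have chosen at random beforehand and moved to 50/30/20 through teaching. Expected score: 20 × (0.50 − 0.20) = +6. The change from baseline is 6 − 0 = +6.

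The recorded score has the same distribution in both. Only the unrecorded baseline tells them apart.

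**Step 3. Within-session change**

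Suppose a player guesses at random for 10 choices, then moves to 50/30/20 for the next 10 because the smile icon has shown what is rewarded. The expected half-scores are 0 and 10 × 0.30 = +3. Genetic learning would give the same rise, and without a comparison group the two cannot be separated.

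**Step 4. Illustration of scores with no learning**

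Exact distribution of the sum by convolution, with independent choices. K and all rates are assumed.

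| Healthy/neutral/unhealthy (%) | Mean, K = 10 / 20 / 40 | P(score > 0), K = 10 / 20 / 40 |
|---|---|---|
| equal thirds | 0 / 0 / 0 | 0.42 / 0.45 / 0.46 |
| 40/35/25 | +1.5 / +3 / +6 | 0.66 / 0.76 / 0.86 |
| 50/30/20 | +3 / +6 / +12 | 0.84 / 0.94 / 0.99 |
| 70/20/10 | +6 / +12 / +24 | 0.99 or higher |

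Hand check of 40/35/25 at K = 20: the variance is 20 × (0.40 + 0.25 − 0.15²) = 12.55, so the SD is 3.54. With a continuity correction, P(score > 0) ≈ Φ((3 − 0.5)/3.54) = Φ(0.71) = 0.76, which agrees.

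The sign needs no particular rates: whenever pH exceeds pU beforehand, the expected score is positive with no learning at all.

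**Step 5. The statements side by side**

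The in-game section says the software can "record changes in the player’s decision-making ability and progress". Materials and Procedures says changes in decision-making abilities in the light of the new knowledge cannot be directly verified. The Limits section first restricts the study to information acquisition and leaves the use of new knowledge in unknown situations to later work; it then reads game achievements as showing how users apply their knowledge.

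**The case against.** The strongest reply is that little rests on this score. Materials and Procedures draws the efficacy conclusions from the questionnaires, Data Analysis for Substudy 2 plans an effect size for knowledge transfer, and the Discussion makes increased knowledge the main endpoint. The in-game section precedes both substudies and mostly describes how the software gives feedback. The Limits sentence promises only some evidence, straight after conceding that the design cannot separate the games' contributions. All of this stands, and it makes the point minor. It does not remove it, because both places still state an inference that the data cannot carry.

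A reader might infer four stronger things that the documents do not support:

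- **That genetic knowledge plays no part in the score.** The list of choices is not given. The Figure 6 caption describes a decision on whether the avatar talks to his doctor about genetic risk, and the Adventure Game section mentions chances to clarify the genetic result. Some choices may draw on genetic content. What is not shown is that the score isolates it.
- **That the score will stand in for the skills element of the Primary Aim.** No section makes that link.
- **That a falsely significant result is built in.** No test against zero is planned, and zero is not named as a benchmark. Assuming a preference for healthy options and then finding a positive mean is partly circular, so the figures illustrate the mechanism and no more.
- **That the article flatly contradicts itself on decision-making.** The statement in Materials and Procedures can be read as concerning participants' own lives, and the in-game section as concerning logged choices. Both could then be true. The wording is in tension and needs reconciling.

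**Conclusion.** The concern holds as a minor point of interpretation. The Gene Adventure score has no pre-game value and no control value, rates choices by healthiness, and follows immediate feedback. It cannot distinguish knowledge gained from the games from prior health common sense or from learning the game's reward rule. That conclusion rests on the described design and needs no assumed rates.

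The size cannot be fixed from the document. Under the assumed rates, a player who learned nothing ends above zero with probability from 0.42 (random choice, 10 choices) to 0.99 or higher (strong prior preference for healthy options). This range assumes independent choices and a simple sum. The questionnaire comparison between arms is untouched.

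**What to change.** Reconcile the in-game assessment section, Materials and Procedures, and Limits and Future Proposal with one statement: the Gene Adventure score describes play in the game arm and will not be used as evidence of knowledge transfer, changed decision-making or applied knowledge; those conclusions rest only on the pre/post questionnaire comparison between arms. Retitle the in-game section to match.

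If the logged choices are to be used, one option is to report, within the game arm, the association of the in-game score with the genetic-risk items of the posttest, adjusted for the same items at pretest and labelled exploratory. With 30 players it will be imprecise, and it would not show that the games caused the learning.

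The cost is wording and the loss of one supportive claim. No new data are needed.
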